## 7.2 STUDY DRUG DOSAGES

Each patient will receive a single dose of 10 mCi I-131-CLR1404 (total mass dose ranging from 0.24 mg to 0.43 mg depending on the day of calibration and injection) through a freely-running peripheral intravenous catheter over a period of at least 10 minutes. The dose selection of 10 mCi was based on organ and whole body radiation dose estimates for I-131-CLR1404 determined from dosimetry studies performed in normal nude mice. These studies indicate that a 10 mCi dose of I-131-CLR1404 provides an acceptable range of organ dosimetry, approximately 2.68 rem/mCi. (An effective dose of 26.8 rem per 10 mCi is an approximate equivalent to the effective dose from 10 CT scans of the abdomen and pelvis.) The physics of imaging I-131 gamma photons predict that 10 mCi will be an adequate dose to obtain good dosimetry images and calculations over a period of 14 days.

Vital signs, including SaO2, will be monitored pre-infusion, 5, 15, 30, and 60 minutes post infusion, and 4-6 hours post infusion. Patients will be observed for toxicity until their final visit at Day 42 post infusion.

**See Nuclear Medicine and Radiopharmacy Instruction Manual for details on infusion of study drug.**

**If a patient withdraws from the study prematurely, (s)he will be strongly encouraged to continue taking thyroid protection medications for 14 days after the infusion of I-131-CLR1404.**

## 7.3 TREATMENT DURATION

Patients will be observed for safety until study completion on Day 42. However, after 30 days on study if the patient is not experiencing any drug-related toxicity, based on the Investigator's discretion, the patient can continue further treatment with a clinically appropriate non-investigational therapy. While on therapy all efforts must be made to collect additional safety assessments until study completion on Day 42.

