## 5. STUDY DESIGN

### 5.1 STUDY SUMMARY

This will be a multi-center study evaluating dosimetry and safety for up to nine patients with refractory or relapsed advanced solid tumors who have failed standard therapy or for whom no standard therapy exists. Patients who are eligible will be infused with a single dose of 10 millicuries (mCi) of I-131-CLR1404. All patients will be prescribed thyroid protection medication to be taken 24 hours prior to injection of the study drug and for 14 days afterwards.

**Patients who withdraw from the study prematurely will be strongly encouraged to continue their thyroid protective medication for the full 14 days post infusion.**

Whole body imaging for dosimetry calculations will be performed at 15-35 minutes post injection; 4-6, 18-24, 48, 72, and 144 hours (Day 6) post injection, and on Day 14 post injection. At the Investigator's discretion, optional SPECT imaging may be obtained between Day 3 and 14 to further characterize the patient's tumor(s). Blood and urine will be collected for clinical laboratory evaluation pre-dose and on days 6, 14, 30 and 42. Blood will be drawn for evaluation of lipids pre-dose and at 72 hours post injection. Blood will be collected for pharmacokinetic analysis prior to dosing, and at 5, 15, 30, and 60 minutes; 4-6, 18-24, 48, and 72 hours; 6, 14, 30, and 42 days post infusion. Blood will be collected for radiologic biodistribution at pre-injection, 15 and 60 minutes, 4-6, 18-24, 48, and 72 hours; 6, 14, 30 and 42 days post dose. Patients will be asked to collect all of their urine for 14 days post injection in order to evaluate the urinary clearance of I-131-CLR1404. Patients will be monitored at each visit for adverse events and the use of concomitant medications.

Patients must have a refractory or relapsed advanced solid tumor and have a sufficient window of time to complete the washout period of 2 weeks if they have received standard therapy or 4 weeks if they have received experimental therapy, the dosimetry data acquisition (14 days), and the follow-up safety assessment period (4 weeks) prior to beginning another cycle of a therapeutic regimen. If, after 30 days on study the patient is not experiencing any drug-related toxicity, the patient can continue further treatment with a clinically appropriate non-investigational therapy, at the discretion of the Investigator.

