### 6.3 INCLUSION CRITERIA

Patients may be enrolled into this protocol only if all of the following inclusion criteria are met:

- Patients must have relapsed or refractory advanced solid tumor and have exhausted standard treatment options or no standard therapy exists for the patient.
- Patients must have a sufficient window of time to complete the washout period of 2 weeks if patients have received standard therapy or 4 weeks if patients have received experimental therapy, dosimetry data acquisition,(14 days), and the follow up safety assessment period (4 weeks) prior to beginning another cycle of a therapeutic regimen.
- Patient is ambulatory with an ECOG performance status of 0 or 1 (Appendix C), and an estimated life expectancy of  $\geq 4$  months.
- Patient is 18 years or older
- Patient is judged by the Investigator to have the initiative and means to be compliant with the protocol and be within geographical proximity to make the required study visits.
- Patients or their legal representatives must have the ability to read, understand and provide written informed consent for the initiation of any study related procedures.
- Patients with brain metastasis are acceptable if the clinical condition has been stable for at least one month. For patients with brain metastasis or glioblastoma multiforme who require steroids, they must have been on a stable or tapering dose of corticosteroids for at least one month.
- Female patients of childbearing potential must have a negative serum pregnancy test within 24 hours of start of treatment.
- Patients must agree to use an effective method of contraception (e.g., oral contraceptives, double-barrier methods such as a condom and a diaphragm, intrauterine device, Norplant, Depo-Provera) during the study and for 90 days following the last dose of study medication.

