### 7.6 *CONCOMITANT MEDICATIONS AND TREATMENTS*

All intercurrent medical conditions will be treated at the discretion of the Investigator according to acceptable community standards of medical care. All concomitant medications and treatments will be documented on the appropriate case report form.

The following medications are not permitted during the study:

- Any other investigational treatment
- Any cytotoxic chemotherapy
- Any other systemic antineoplastic therapy including, but not limited to, immunotherapy, or monoclonal antibody therapy. (Ongoing treatment with hormonal therapy may be continued during the trial.)
- Systemically administered radioisotope therapy.
- Prophylactic hematopoietic growth factors, particularly filgrastim, peg-filgrastim and oprelvekin, should be avoided if at all possible during the study. Of course, patient safety must remain paramount, and if in the Investigator's opinion, such therapy is required during the study, growth factors should be used according to current ASCO guidelines. Medroxyprogesterone may be given to patients as an appetite stimulant.

Palliative external beam radiation therapy for bone pain is allowed at the Investigator's discretion, consistent with allowable limits previously stated.

The metabolism of I-131-CLR1404 is not completely understood. There are no known interactions with other medications.

Previous human studies have demonstrated that I-131-NM404, a compound closely related to I-131-CLR1404, has a plasma half-life of 113 hours, and less than 10% urinary excretion over 96 hours. Preclinical studies indicate that CLR1404 is primarily excreted through the hepatobiliary system (33%) over several half-lives of the drug.

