## 10. PATIENT WITHDRAWAL

### 10.1      *CRITERIA FOR PATIENT WITHDRAWAL*

Patients may withdraw their consent to participate in the study at any time without prejudice to his/her future medical care by the physician or at the institution.

If a patient withdraws consent, the date and reason for consent withdrawal should be documented. Patient data will be included in the analysis up to the date of the consent withdrawal.

Wherever possible, the tests and evaluations listed for the final visit should be carried out. The sponsor should be notified of all study withdrawals in a timely manner.

Patients may be removed from the study if any one or more of the following events occur:

- Patient withdrawal of consent
- Dose limiting toxicity
- Discretion of Principal Investigator (reason to be documented on CRF)
- Patient becomes pregnant or begins breast-feeding
- Patient lost to follow-up (defined as the inability to contact the patient on two separate occasions over a period of 1 week)
- Administrative reasons (e.g., the patient is transferred to hospice care)
- An adverse event, which in the opinion of the Investigator, precludes further study participation or fulfills the protocol requirements for withdrawal (e.g., the development of dose limiting toxicity)
- Patient develops an intercurrent illness that precludes further participation, or requires a prohibited concomitant treatment

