#### *11.5 STATISTICAL ANALYSIS*

All baseline patient characteristics will be summarized in a tabular format.

Safety data will be described for all patients receiving an infusion of I-131-CLR1404. Safety data will include values for hematology, serum chemistry, urinalysis and vital signs, results of ECG determinations and adverse events. The proportion of patients experiencing adverse events will be reported and SAEs will be summarized.

The I-131-CLR1404 plasma concentration-time data will be determined for each patient. The following PK parameters will be determined:

$C_{\max}$   
AUC (0-144hr)  
Plasma half-life ( $t_{1/2}$ )  
Plasma clearance (Cl)  
Vd

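### Sections 5.1 and 7.3 allow a new therapy after Day 30, while 7.6 and 6.4 rule out systemic anticancer therapy on a study that ends on Day 42; in patients who switch, late safety data can reflect either treatment.

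*Protocol*

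**What the plan says.** **Permission.** Section 5.1 opens it with "If, after 30 days on study the patient is not experiencing any drug-related toxicity", and 7.3 repeats it: if the Investigator agrees, "the patient can continue further treatment with a clinically appropriate non-investigational therapy".

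**End of study.** Section 7.3 states "Patients will be observed for safety until study completion on Day 42" and foresees the overlap: "While on therapy all efforts must be made to collect additional safety assessments until study completion on Day 42".

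**Prohibition.** Section 7.6 heads its list "The following medications are not permitted during the study". The list includes cytotoxic chemotherapy and other systemic antineoplastic therapy. It gives no end date before study completion. Its stated allowances cover ongoing hormonal therapy, growth factors when needed, medroxyprogesterone for appetite and palliative radiotherapy for bone pain. Therapy after Day 30 is not among them.

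**Eligibility.** Section 6.4 excludes patients for whom chemotherapy, therapeutic radiation or biological cancer treatment is planned on study. Sections 5.1 and 6.3 require time for washout, 14 days of dosimetry and "the follow up safety assessment period (4 weeks) prior to beginning another cycle of a therapeutic regimen".

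**Analysis.** Section 11.5 says "Safety data will be described for all patients receiving an infusion of I-131-CLR1404". It reports the proportion of patients with adverse events and mentions no cut at the start of another therapy.

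**The concern.** A site that reads 7.3 would take chemotherapy on Day 31 as allowed. A site that reads 7.6 would take it as a violation. With about four sites and up to nine patients, different readings would give patients different exposure in the last part of follow-up.

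Safety is a secondary objective. A fall in counts on Day 42, or an adverse event starting after Day 30, may come from the study drug or from the next regimen. The relatedness judgement in 9.4.2 helps with individual adverse events. It does nothing for the overall proportion of patients with adverse events, or for the Day 42 laboratory values, because neither is filtered by cause.

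The mixing is also selective, since only patients without drug-related toxicity at Day 30 may switch.

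**Working it through.** The protocol gives no sample size, power or error rate to reproduce (11.3). The check is a comparison of text plus date arithmetic.

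**1. Do the rules conflict?**
- Sections 5.1 and 7.3: therapy may start after Day 30, and the patient stays in follow-up to Day 42.
- Section 7.6: systemic anticancer therapy is barred during the study, and 7.3 ends the study on Day 42.
- Section 6.4: a plan for such therapy on study excludes the patient.

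The permission could be confined to treatments that 7.6 does not bar. It would then add little, because ongoing hormonal therapy and palliative radiotherapy are already allowed. Section 5.1 also places it directly after the sentence on another treatment cycle. The conflict stands.

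**2. Window at entry against Day 30** (5.1, 6.3, 7.3)
- Dosimetry plus safety period: 14 + 28 = 42 days, which matches the final visit.
- Permission: after 30 days.
- If the 4 weeks are counted from infusion, they end on Day 28 and this tension disappears. The conflict with 7.6 and 6.4 does not.

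**3. Follow-up open to mixing**
- 42 − 30 = 12 days; 12/42 = 28.6%.
- With the ±2-day window on the final visit in the 8.1 schedule: 40 − 30 = 10 to 44 − 30 = 14 days.

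**4. Blood counts** (8.2.3.8: post-dose Days 6, 14, 30 and 42)
- Days 6 and 14 cannot be affected, nor can a Day 30 count drawn before the new therapy starts.
- Day 42 can be: one of four post-dose counts, one of two after Day 14, and the only one after Day 30.

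**5. What a loss of clean Day 42 observations means**

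The number who switch is not given, so this is an assumed range. If no event is seen in n patients free of new therapy at Day 42, the one-sided 95% upper bound on the event rate is 1 − 0.05^(1/n):

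| Patients free of new therapy at Day 42 | Upper bound |
|---|---|
| 9 | 28.3% |
| 6 | 39.3% |
| 3 | 63.2% |

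**6. Dosimetry**

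Whole-body imaging and urine collection end at Day 14, and 5.1 gives 14 days for dosimetry data. Blood for biodistribution is still drawn on Days 30 and 42. With the 8.02-day physical half-life in 7.1, however, decay alone leaves 2^(−30/8.02) = 7.5% of the activity by Day 30 and 2^(−42/8.02) = 2.7% by Day 42.

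**The case against.** The best defence is that 7.3 is a deliberate exception. It is specific, conditional, repeated in 5.1, and it asks for safety assessments to continue on the new therapy. A site could probably work out what was meant. That makes this a drafting fault rather than a confused design. It does not remove the conflict, because 7.6 lists its own allowances and omits this one, and 6.4 has no matching carve-out.

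It is also fair that 7.6 already puts concomitant treatments on the case report form, that adverse event onset dates are recorded, and that the rule for tabulation may sit in a statistical analysis plan that is not shown. Data before and after a switch should therefore be largely separable. An analysis plan cannot settle eligibility and prohibited-treatment wording, though.

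A reader might infer more than the documents support:
- **Switching is a ground for removal under 10.1.** The item reads "Patient develops an intercurrent illness that precludes further participation, or requires a prohibited concomitant treatment". It is framed around intercurrent illness, in a list of reasons for which patients may be removed. Planned next-line therapy is not clearly covered.
- **Section 6.3 forbids therapy before Day 42.** It is an entry test of available time, not a ban.
- **Palliative radiotherapy is part of the same contradiction.** Sections 6.4 and 7.6 both allow it for bone pain, and it is not tied to Day 30.
- **All nine patients are affected.** That is a ceiling. It would need every patient to qualify and switch.
- **The two-patient stopping rule in 10.2 would be triggered wrongly.** That rule counts only toxicities related to the study drug, and no rate of misattribution is given.
- **Selection biases the whole safety picture.** It works both ways: under 5.1 and 7.3, patients with drug-related toxicity at Day 30 may not switch, so their late data stay free of new therapy.

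**Conclusion.** The point holds at moderate severity. Sections 5.1 and 7.3 contradict 7.6 and 6.4 on systemic anticancer therapy between Day 30 and Day 42, and 5.1 and 6.3 add a tension of 42 days against 30.

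In patients who switch, the exposed data are adverse events with onset in up to the last 12 of 42 days and the Day 42 laboratory values, including the only scheduled blood count after Day 30. This is an upper limit per patient: it assumes that therapy starts directly after Day 30. The number of patients concerned lies between none and nine, and the protocol gives no basis for narrowing it.

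A reader might go on to infer that the trial's main result is at risk. It is not. Dosimetry and the marrow-based dose rest on data collected over 14 days, and safety is a secondary, descriptive endpoint in a study that 11.3 calls hypothesis generating.

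**What to change.** 1. Reconcile 5.1, 6.3, 6.4, 7.3 and 7.6 so that they give one answer on whether systemic anticancer therapy may start before Day 42. Which rule should stand is for the sponsor. State from which day the 4-week safety period is counted.
2. If such therapy may start before Day 42, add to 11.5 that the main safety summary covers adverse events with onset, and laboratory values taken, before its first dose. List later data separately. If the statistical analysis plan already does this, a cross-reference is enough.
3. Take the start date from the concomitant-treatment page of the case report form, which 7.6 already requires.

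The cost is protocol wording and one date flag in the safety tables. The downside is small: fewer Day 42 values in the main safety table, with the removed values still visible in the listing.

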## 7.4 PATIENT REPLACEMENT

Patients who withdraw from the study within 14 days of infusion will be replaced and will be encouraged to return to the clinical site for further follow-up care for the purposes of safety assessment. Patients will be strongly encouraged to continue their thyroid protection medication for 14 days after the infusion of study drug.

### 7.5 *STUDY DRUG ACCOUNTABILITY*

The clinical site staff must maintain a careful inventory of the study drug. Study drug use will be recorded on a study drug inventory form. At a minimum, this form will contain the following information:

- Patient number and initials for each patient receiving study drug
- Date, quantity and dose (mCi) of study drug received by the clinical site
- Date, quantity and dose (mCi) of study drug dispensed
- Date, quantity and dose (mCi) administered

At each monitoring visit, Collectar's clinical monitor will reconcile the information on the study drug inventory form with the actual inventory of study drug used at each clinical site. All used and expired radioactive vials of I-131-CLR1404 will be stored at the clinical site in long half-life radioactive storage per the clinical site's standard operating procedures (SOPs) until background levels are reached, approximately 80 days. When the used vials are no longer radioactive, drug accountability will be conducted by the clinical monitor and the vials will be shipped to Collectar for disposal or discarded by the clinical site as per their SOP.

### 7.6 *CONCOMITANT MEDICATIONS AND TREATMENTS*

All intercurrent medical conditions will be treated at the discretion of the Investigator according to acceptable community standards of medical care. All concomitant medications and treatments will be documented on the appropriate case report form.

The following medications are not permitted during the study:

- Any other investigational treatment
- Any cytotoxic chemotherapy
- Any other systemic antineoplastic therapy including, but not limited to, immunotherapy, or monoclonal antibody therapy. (Ongoing treatment with hormonal therapy may be continued during the trial.)
- Systemically administered radioisotope therapy.
- Prophylactic hematopoietic growth factors, particularly filgrastim, peg-filgrastim and oprelvekin, should be avoided if at all possible during the study. Of course, patient safety must remain paramount, and if in the Investigator's opinion, such therapy is required during the study, growth factors should be used according to current ASCO guidelines. Medroxyprogesterone may be given to patients as an appetite stimulant.

Palliative external beam radiation therapy for bone pain is allowed at the Investigator's discretion, consistent with allowable limits previously stated.

The metabolism of I-131-CLR1404 is not completely understood. There are no known interactions with other medications.

Previous human studies have demonstrated that I-131-NM404, a compound closely related to I-131-CLR1404, has a plasma half-life of 113 hours, and less than 10% urinary excretion over 96 hours. Preclinical studies indicate that CLR1404 is primarily excreted through the hepatobiliary system (33%) over several half-lives of the drug.

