##### 4.2 SECONDARY OBJECTIVES

The secondary objectives of the study are:

- To determine the safety of I-131-CLR1404
- To determine the pharmacokinetic profile of I-131-CLR1404

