#### 8.2.3.11 *Pharmacokinetic Analysis*

Blood will be drawn for plasma PK analysis at pre-treatment, 5, 15, 30, and 60 minutes post infusion, at each imaging visit, and on Days 14, 30 and 42. Blood samples for plasma PK analysis will be collected into EDTA (lavender top) anticoagulation tubes at each time point. Samples should be centrifuged and plasma collected, equally divided into two separate aliquots, and placed in 2 ml cryovials. Shipping materials will be provided for frozen shipment to Collectar. For detailed instructions on handling PK samples refer to the Covance laboratory manual and the Laboratory and Biodistribution Manual.

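### The only AUC named stops at 144 hours, although plasma sampling runs to Day 42; at the one half-life the protocol gives, it is expected to capture about 59% of total exposure

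*Protocol*

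**What the plan says.** Section 4.2 makes PK a secondary objective: "To determine the pharmacokinetic profile of I-131-CLR1404".

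Section 11.5 introduces its list with "The following PK parameters will be determined". The list is Cmax, AUC(0-144hr), plasma half-life, clearance and Vd. No other AUC is named, no reason is given for stopping at 144 hours, and nothing says how clearance or Vd is derived.

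Sampling goes much further. After the first hour, section 5.1 schedules plasma PK draws at "4-6, 18-24, 48, and 72 hours; 6, 14, 30, and 42 days post infusion". Section 8.2.3.11 agrees: "at each imaging visit, and on Days 14, 30 and 42". The Day 30 and Day 42 visit lists in section 8.2.2 also include a PK draw.

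Section 7.6 holds the only plasma half-life in the protocol. It comes from human studies of I-131-NM404, a close relative of the study drug, which "has a plasma half-life of 113 hours".

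**The concern.** The integration limit in section 11.5 does not match the sampling schedule or the half-life in section 7.6. The 144-hour limit is Day 6. Three of the 13 scheduled PK samples (Days 14, 30 and 42) fall after it and cannot enter the AUC. With a half-life near 113 hours, a large part of the area lies beyond the limit.

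Two things are at stake for the secondary objective:

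- The reported AUC would understate total exposure.
- The missing share grows with a patient's half-life, so it is not a constant factor that can be rescaled afterwards. Slow eliminators would look closer to average than they are. With at most nine patients, the spread between individuals is a large part of what the PK data can show.

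**Working it through.** The protocol states no AUC coverage, so there is no figure of its own to reproduce.

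**Inputs**

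- Half-life T = 113 h, for I-131-NM404 (section 7.6).
- AUC limit t = 144 h (section 11.5).
- Late samples at Days 14, 30 and 42, which are 336, 720 and 1008 h (section 5.1).
- Physical half-life of I-131, 8.02 days × 24 = 192.5 h (section 7.1), for sensitivity only.

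**Fraction of total AUC captured.** Under mono-exponential decline, F(t) = AUC(0-t)/AUC(0-infinity) = 1 − 2^(−t/T).

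- 144/113 = 1.27 half-lives, and 2^(−1.27) = 0.413, so F(144) = 0.587. About 41% of the area is still to come.
- F(336) = 0.873, F(720) = 0.988 and F(1008) = 0.998.
- The Day 14 sample alone accounts for most of the gain: 0.873 − 0.587 = 0.286.

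**Sensitivity of F(144)**

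| Assumption | Captured by 144 h |
|---|---|
| Draw at 138 h or 150 h (the ±6 h window), T = 113 h | 57.1% or 60.2% |
| 10-minute infusion instead of a bolus | 58.7% |
| T = 80, 100, 130, 150 h (assumed) | 71%, 63%, 54%, 49% |
| A fast phase holding 10% to 30% of the AUC (assumed) | 63% to 71% |
| 113 h is biological and activity is not decay-corrected: T = 1/(1/113 + 1/192.5) = 71.2 h | 75% |
| 113 h is already effective, so decay-corrected T = 1/(1/113 − 1/192.5) = 273.7 h | 31% |

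Across these scenarios the range is about 31% to 75%, so about a quarter of total exposure or more is missed in each.

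**Compression between patients.** Take two patients with equal dose and volume and assumed half-lives of 80 h and 150 h.

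- Total AUC is proportional to T: 150/80 = 1.88-fold difference.
- AUC(0-144hr) is proportional to T × F: (150 × 0.486)/(80 × 0.713) = 72.9/57.0 = 1.28-fold difference.

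**Clearance and Vd, only if AUC(0-144hr) were used for them**

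- Cl = dose/AUC would be 1/0.587 = 1.70 times too high at T = 113 h.
- Vd = Cl/λ, with λ estimated separately, would be inflated by the same factor.
- Vd = dose/C0 uses no AUC and would be unaffected.
- Vss = dose × AUMC/AUC², with both truncated at 144 h, gives (1 − 0.413 × 1.883)/0.587², or about 0.64 of the true value. Here 1.883 = 1 + ln 2 × 144/113.

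The direction of any error in Vd therefore depends on the estimator.

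**The case against.** The other side has a good deal that stands.

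- **Clearance and Vd.** A reader might infer that both will be overstated. The protocol does not support that. Section 11.5 lists them as separate parameters and never ties them to AUC(0-144hr). How they are derived is commonly left to a statistical analysis plan, which was not available here. The 1.70-fold figure is conditional, and the working shows that Vd could go either way.
- **The half-life.** The 113 hours belongs to a related compound, and section 7.6 says the metabolism of I-131-CLR1404 is not fully understood. So 59% is an expectation under a simple model.
- **Wasted samples.** A reader might infer that the late draws go unused. They are left out of this AUC only and can still inform half-life, clearance and Vd.
- **Only exposure measure.** That would be too strong, since Cmax is also listed. AUC(0-144hr) is the only AUC.
- **Drug remaining.** The 0.413 is plasma concentration relative to its starting value, or equally the share of area still to come. It is not the share of drug still in plasma.
- **Consequence.** The starting dose for the next study comes from OLINDA dosimetry, based on imaging, blood sampling and urine (sections 5.1 and 11.4), with separate biodistribution blood samples (section 8.2.3.12). No passage makes it depend on plasma AUC. No between-patient comparison of exposure is planned, and section 11.3 calls the study hypothesis-generating.
- **A fixed interval has merits.** Day 6 is the last visit with a ±6 h window; later windows are in days. At T = 113 h, concentration falls to 12.7% of its initial value at Day 14, 1.2% at Day 30 and 0.2% at Day 42. The protocol gives no assay limit, so the last samples may not be quantifiable and AUC(0-last) could end at different times in different patients.

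These points limit the consequence and argue for keeping the 144-hour AUC. They do not explain why it should be the only one. Even if the Day 30 and Day 42 samples were below the assay limit, integrating to Day 14 would be expected to capture 87%.

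**Conclusion.** The point holds as a mismatch between a stated analysis choice and the protocol's own schedule and half-life. A statistical analysis plan could add other AUCs, but section 11.5 itself fixes the interval and names no other. Following it as written gives a truncated measure of exposure for a secondary objective: about 59% of the total, assuming mono-exponential decline at 113 hours, and about 31% to 75% across the assumptions examined on half-life and decay correction. It also compresses between-patient differences in total exposure.

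The finding does not extend to an asserted error in clearance or Vd, or to the primary dosimetry endpoints. It is worth correcting because the samples that would give total exposure are already scheduled.

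**What to change.** In section 11.5:

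- Add AUC(0-infinity) and AUC(0-last), the latter using all quantifiable samples through Day 42, as the measures of total exposure. Report the extrapolated fraction for each patient.
- State that clearance is dose/AUC(0-infinity), and that any Vd calculation needing an AUC or a clearance is on the same basis.
- Keep AUC(0-144hr) as a fixed-interval partial AUC. It gives a common interval for all patients if AUC(0-last) ends at different times.

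The cost is a short text change and a little more analysis. No extra draws, visits or patients are needed. Some late samples may fall below the assay limit, and the extrapolated fraction will show where that matters.
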